#### Intervention Arm

In the intervention arm, the eRegistry supported 3 data-driven DHIs linked to the digital client health records (Table 1) as follows: (1) for facility-based staff, health worker clinical decision support based on national guidelines to promote the correct management of health conditions identified in antenatal care; (2) for both field- and facility-based staff, feedback dashboards tracking the health worker’s progress toward pregnancy registration, antenatal care attendance and utilization, and clinical screening and management targets; and (3) for pregnant women, targeted client communication in the form of SMS text messages to address gaps in the timely attendance of antenatal care visits and facility delivery. Following the initial implementation of the eRegistry, the DHIs in the intervention arm were gradually introduced over the course of the trial; health worker clinical decision support was introduced in October 2018; targeted client communication via SMS and feedback dashboards were implemented in June 2019. Digital client health records were accessible across the cadres of health workers, facilities, and arms of the health system for a comprehensive longitudinal tracking of clients’ health status and services received (Table 1).

Guideline-based clinical decision support and feedback dashboards were developed in close collaboration with health workers. The decision support comprised referral and counseling reminders, medication alerts, and scheduling based on the recommended guidelines in the public health system. Feedback dashboards were customized for each cadre of health workers, with indicators of antenatal care attendance and screening and management of gestational diabetes, hypertension, and anemia. Targeted client communication included SMS text message reminders of routine antenatal care, referral facilitation SMS text messages for those at risk, and facility delivery reminders for those who are advised to have an institutional delivery. All DHIs were triggered by data entry into the eRegistry at the point of care by the health workers.

### Adherence

The Directorate General of Health Services in Bangladesh employs DHIS2 as their national health information system platform for aggregate data. A DHIS2 tracker app for individual-level data collection is available for one cadre of health workers, the community health care providers. The study team reinforced adherence to the use of the eRegistry in several ways. The study team members periodically attended monthly meetings with health workers. Technical support was provided for crosscutting issues around data entry, client identification, and verification to both the control and intervention arms throughout the trial. After the rollout of the eRegistry, all health workers were evaluated on key competencies in using the eRegistry and the Element biometrics app. Those identified with challenges in using digital tools were retrained. Field support staff from the study team also checked in periodically on such health workers to provide one-on-one support. The study team maintained a log of the most important issues that emerged with a possible direct impact on trial outcomes. Key indicators of adherence to the use of the eRegistry across intervention and control clusters will be presented along with the trial results.

### Concomitant Care

At the start of the trial, no other health information system studies or implementations were ongoing in the study area. Both the control and intervention arms of the trial received similar support in the use of the eRegistry for data entry. Intervention and control clusters offer the same clinical antenatal care services, and the national treatment and management guidelines set by the Ministry of Health and Family Welfare for maternal and child health apply to both. All health facilities in the Matlab North Upazila are a part of separate demand-side incentive programs to encourage women to attend antenatal and postnatal care and to have a facility delivery [19]. During the postpartum home visit, we will capture data that allow the estimation of the proportion of women who utilized these programs and subsequently account for possible effects of this on the trial outcomes.

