### Outcomes

The outcomes were formulated based on their relevance to the health system context and were meant to capture the potential effects of the specific DHIs under assessment. Data for the primary (Table 2) and secondary outcomes (Table 3) will be derived from the eRegistry’s client health records and through postpartum home visit interviews.

**Table 2 table2:** Primary outcomes, data sources, and definitions.

Primary outcome	Sources of data	Measurement sequence	Definition	Intervention subcomponents with most direct effect
Timely attendance at eligible ANC^a^ visits	Postpartum household survey	Registrations continuously at point of care Household visit after the completion of pregnancy	Proportion with timely attendance	Targeted Client Communication via SMS text message: ANC appointment reminders
Screening and management for hypertension in pregnancy	Case records from the eRegistry^b^	Registrations continuously at point of care	Proportion that has at least one ANC at a randomized health facility with: Blood pressure measurement at routine ANC visits, and Referred if blood pressure is high, or Referred if blood pressure is high outside of the routine ANC visit	Health worker clinical decision support Feedback dashboards with action items

^a^ANC: antenatal care.

^b^eRegistry: electronic registry.

**Table 3 table3:** Secondary outcomes, data sources and definitions.

Secondary outcome	Sources of data	Measurement sequence	Definition	Intervention subcomponents with assumed direct effect
Timely first ANC^a^ visit	Case records from the eRegistry^b^ Postpartum household survey	Registrations continuously at point of care Household visit after the completion of pregnancy	Proportion of women that have an ANC visit at or before 16 weeks among those with a home pregnancy registration before 16 weeks	Targeted Client Communication via SMS text message: ANC appointment reminders
High-risk women successfully referred to a skilled provider for additional care	Case records from the eRegistry Postpartum household survey	Registrations continuously at point of care Household visit after the completion of pregnancy	Proportion of women that received additional care during pregnancy among those that are referred for severe anemia, or hypertension or diabetes during pregnancy	Health worker clinical decision support Targeted client communication via SMS: Referral reminders, high risk, facility delivery reminders

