Facility delivery among those advised to deliver in a facility	Case records in the eRegistry Postpartum household survey	Registrations continuously at point of care Household visit after completion of pregnancy	Proportion of women that deliver in a facility among those that should delivery in a facility based on certain risk factors identified during ANC	Health worker clinical decision support Targeted client communication via SMS text message: high risk, facility delivery reminders
Births with severe morbidity or mortality among all women and among those with any risk identified	Case records in the eRegistry Postpartum household survey	Registrations continuously at point of care Household visit after completion of pregnancy	Proportion with a very preterm birth, very low birth weight, perinatal death, or hospitalization of the newborn for at least 7 days after birth among all women enrolled in the trial, and those with any identified risk during ANC	Health worker clinical decision support Targeted client communication via SMS text message: referral reminders
Severe postpartum anemia	Postpartum household survey	Household visit after the completion of pregnancy	Proportion of women with severe anemia in postpartum	Health worker clinical decision support Targeted client communication via SMS text message: referral reminders

^a^ANC: antenatal care.

^b^eRegistry: electronic registry.

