### Allocation

#### Randomization of Health Facilities

The unit of randomization was a health facility (community clinics or family welfare clinics) located in the study area, which provided antenatal, childbirth, and postpartum care. We performed stratified restricted randomization with a 1:1 ratio. The randomization was stratified based on the type of clinic (family welfare clinics and community clinics) and whether the facility was staffed with a care provider. The randomization within each stratum was then restricted based on (1) the clinic’s allocation as intervention or control within a preceding project in the study area for strengthening maternal and child health services; (2) the technological skills of the staff; (3) the monthly number of clients attending the clinic; and (4) the monthly number of antenatal care visits. To measure the technological skills of the staff, we created an index using information from a provider and a clinic survey conducted by the study team in preparation for the trial. The index included items such as health workers’ technological capabilities, such as the use of phones for SMS and internet, and their comfort using technology. Statisticians at the Centre for Intervention Science in Maternal and Child Health (CISMAC), University of Bergen, undertook randomization.

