#### Individual Women Within the Trial

The family welfare assistant enrolled individual women in the trial at pregnancy identification and registration. At that time, women were required to provide informed consent to receive communication from the study team and a home visit 8-14 days after the birth of the child (Figure 2). Women were then asked about their preferred public health facility for antenatal care, which determined allocation to an intervention or control cluster (Figure 3). Women may also be first identified as pregnant at a health facility. At this contact, women were registered in the eRegistry and automatically assigned to an intervention or control cluster based on the allocation status of that health facility (Figure 3). After completion of the pregnancy, the data collection team conducted a postpartum home visit within 8-14 days of birth for collection of outcome data.

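### The protocol plans to account for the Matlab North incentive programs through women's program use recorded after birth; Upazila, known before randomization, is the safer variable and should be prespecified

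*Protocol article*

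**What the plan says.** Concomitant Care states that "All health facilities in the Matlab North Upazila are a part of separate demand-side incentive programs", whose purpose is "to encourage women to attend antenatal and postnatal care and to have a facility delivery". It then says that the team intends to "capture data that allow the estimation of the proportion of women who utilized these programs and subsequently account for possible effects of this", meaning effects on outcomes. The data come from the postpartum interview; under Individual Women Within the Trial, "the data collection team conducted a postpartum home visit within 8-14 days of birth for collection of outcome data".

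The intervention works on the same behaviours. Its SMS component is meant "to address gaps in the timely attendance of antenatal care visits and facility delivery" (Intervention Arm). Timely antenatal attendance is a primary outcome (Table 2), and "Facility delivery among those advised to deliver in a facility" is a secondary outcome (Table 3).

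On allocation, "The randomization was stratified based on the type of clinic" and on whether the facility had a care provider. Four restriction factors follow: allocation in a preceding project, staff technological skills, monthly clients and monthly antenatal visits. Upazila is in neither list. Statistical Methods allows confounder adjustment in the primary analysis only for important imbalance at baseline, which it identifies by a change of more than 5% in the effect measure.

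**The concern.** The variable named for handling the programs is women's use of them. It is observed after allocation, after antenatal care and after delivery. Messages that raise attendance may also raise use of a program that encourages attendance. Use would then lie on, or downstream of, the path from allocation to outcome, and conditioning on it would remove part of the effect being estimated.

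The underlying difference between places does not need that variable. Whether the programs exist at a woman's allocated facility depends on whether it lies in Matlab North or South. That is fixed before randomization and cannot be changed by arm. At stake are the estimates for timely attendance and facility delivery, the outcomes that the programs and the SMS messages share.

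**Working it through.** **The plan's figures.** The protocol gives no figure for the programs' effect. The sample-size section gives 20% versus 33% timely attendance, so the target risk ratio (RR) is 0.33/0.20 = 1.65. That section's power statement is not in question. With 77 women per cluster and an intracluster correlation of 0.1, the design effect is 1 + 76 × 0.1 = 8.6. With 29 and 30 clusters and an assumed two-sided 5% level, power is 92.5%, which agrees with the stated figure of more than 80%.

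**Assumptions not in the document.** Half of the women in each arm are in Matlab North, the programs are used only there, and the control rate is 20% in both Upazilas. Uptake in North is u₁ among timely attenders (40-80%) and u₀ among others (5-30%).

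**Formula.** Stratify by program use and take the Mantel-Haenszel RR = Σ(a·n₀/N) / Σ(c·n₁/N). Here a and c are the timely attenders in the intervention and control arms, n₁ and n₀ are the stratum sizes, and N = n₁ + n₀. All are expressed per woman in each arm.

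**Worked case, u₁ = 0.80, u₀ = 0.05.**
- Users, intervention: a = 0.5 × 0.33 × 0.80 = 0.132; n₁ = 0.132 + 0.5 × 0.67 × 0.05 = 0.14875.
- Users, control: c = 0.5 × 0.20 × 0.80 = 0.080; n₀ = 0.080 + 0.5 × 0.80 × 0.05 = 0.100.
- Non-users, intervention: a = 0.33 − 0.132 = 0.198; n₁ = 0.85125.
- Non-users, control: c = 0.20 − 0.080 = 0.120; n₀ = 0.900.
- Numerator: 0.132 × 0.100/0.24875 + 0.198 × 0.900/1.75125 = 0.0531 + 0.1018 = 0.1548.
- Denominator: 0.080 × 0.14875/0.24875 + 0.120 × 0.85125/1.75125 = 0.0478 + 0.0583 = 0.1062.
- RR = 1.46 against a true 1.65.

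**Across the assumed range:**

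| u₁ / u₀ | RR given use | Change from 1.65 |
|---|---|---|
| 0.80 / 0.05 | 1.46 | −11.6% |
| 0.80 / 0.10 | 1.50 | −9.1% |
| 0.60 / 0.05 | 1.52 | −7.9% |
| 0.60 / 0.15 | 1.58 | −4.1% |
| 0.40 / 0.10 | 1.61 | −2.6% |
| 0.50 / 0.30 | 1.64 | −0.7% |
| 0.40 / 0.30 | 1.65 | −0.2% |

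The full range is about 1.46 to 1.65. If use is unrelated to attendance (for example 0.30 / 0.30), the RR stays at 1.65.

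**Upazila instead.** Suppose that control rates are 25% in North and 15% in South, and that chance puts 60% of intervention women but 40% of control women in North.
- Crude RR = 1.65 × (0.6 × 0.25 + 0.4 × 0.15) / (0.4 × 0.25 + 0.6 × 0.15) = 0.3465/0.19 = 1.82.
- With the imbalance reversed, it is 0.3135/0.21 = 1.49.
- Stratifying by Upazila gives 1.65 in both cases.

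**The 5% rule.** In the first three rows of the table, adding program use moves the RR by more than 5%, and that movement is bias rather than correction of an imbalance. A change-in-estimate test cannot tell the two apart.

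**The case against.** The strongest reply is that the protocol names no method. It speaks of estimating a proportion, which is a group-level quantity, and of accounting for possible effects. That could mean a description by arm, a sensitivity analysis or a point of interpretation. A reader might infer that the primary model will include individual program use and that the planned estimate is therefore attenuated. The text does not support that. Statistical Methods confines primary adjustment to baseline imbalance, and a report given after birth is not a baseline variable.

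A reader might also infer that women use the programs because they attended. The document says only that the programs encourage attendance. If enrolment came before care and did not depend on arm, use would be partly a cause of attendance, and conditioning on it would do little harm.

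Nor does the document show that North and South are imbalanced or left unhandled. It gives no Upazila distribution by arm. The baseline-imbalance rule could admit Upazila, and equity analyses by residence are planned, although residence is not defined as Upazila. Any imbalance from the randomization would be a chance one, so the randomized comparison stays unbiased in expectation.

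These points stand, and they limit the concern to a conditional one. They do not remove it. The sentence ties the accounting to women's use, and accounting for effects on outcomes goes beyond describing uptake. As worded, it leaves room for a conditioned analysis. An omitted method is normally left to the analysis plan, but here the variable itself has been named.

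**Conclusion.** The point holds in a limited form. The protocol names a post-allocation variable, linked to the outcomes, as the means of accounting for a factor that place fixes before randomization. If an effect estimate is conditioned on individual use, it is biased whenever use depends on attendance, probably toward the null. Under the stated assumptions, an RR of 1.65 becomes about 1.46 to 1.65, which is a loss of anywhere from nearly nothing to 12%. The uptake rates and the North share are assumed. The calculation covers timely attendance only; for facility delivery the argument is qualitative.

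It does not follow that the trial's primary estimate will be attenuated, or that Upazila is imbalanced between arms. Upazila is not a listed stratification or restriction factor, and it would enter the model only if it passed the 5% rule. That is a weaker position than naming it in advance.

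**What to change.** Replace the open commitment in Concomitant Care with one sentence, and carry it into Statistical Methods:
- The incentive programs are handled by a fixed Upazila term (Matlab North versus South) in the primary models, whatever the 5% rule shows.
- An arm-by-Upazila interaction may be added if it is prespecified.
- Program use is reported descriptively by arm and Upazila.
- Primary and secondary effect estimates are not conditioned on program use; any analysis that does so is labelled exploratory.

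The cost is one extra model term. Upazila is known for every facility, so no new data are needed, and the postpartum questions on program use keep their descriptive purpose.

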### Outcomes

The outcomes were formulated based on their relevance to the health system context and were meant to capture the potential effects of the specific DHIs under assessment. Data for the primary (Table 2) and secondary outcomes (Table 3) will be derived from the eRegistry’s client health records and through postpartum home visit interviews.

**Table 2 table2:** Primary outcomes, data sources, and definitions.

Primary outcome	Sources of data	Measurement sequence	Definition	Intervention subcomponents with most direct effect
Timely attendance at eligible ANC^a^ visits	Postpartum household survey	Registrations continuously at point of care Household visit after the completion of pregnancy	Proportion with timely attendance	Targeted Client Communication via SMS text message: ANC appointment reminders
Screening and management for hypertension in pregnancy	Case records from the eRegistry^b^	Registrations continuously at point of care	Proportion that has at least one ANC at a randomized health facility with: Blood pressure measurement at routine ANC visits, and Referred if blood pressure is high, or Referred if blood pressure is high outside of the routine ANC visit	Health worker clinical decision support Feedback dashboards with action items

^a^ANC: antenatal care.

^b^eRegistry: electronic registry.

**Table 3 table3:** Secondary outcomes, data sources and definitions.

Secondary outcome	Sources of data	Measurement sequence	Definition	Intervention subcomponents with assumed direct effect
Timely first ANC^a^ visit	Case records from the eRegistry^b^ Postpartum household survey	Registrations continuously at point of care Household visit after the completion of pregnancy	Proportion of women that have an ANC visit at or before 16 weeks among those with a home pregnancy registration before 16 weeks	Targeted Client Communication via SMS text message: ANC appointment reminders
High-risk women successfully referred to a skilled provider for additional care	Case records from the eRegistry Postpartum household survey	Registrations continuously at point of care Household visit after the completion of pregnancy	Proportion of women that received additional care during pregnancy among those that are referred for severe anemia, or hypertension or diabetes during pregnancy	Health worker clinical decision support Targeted client communication via SMS: Referral reminders, high risk, facility delivery reminders
Facility delivery among those advised to deliver in a facility	Case records in the eRegistry Postpartum household survey	Registrations continuously at point of care Household visit after completion of pregnancy	Proportion of women that deliver in a facility among those that should delivery in a facility based on certain risk factors identified during ANC	Health worker clinical decision support Targeted client communication via SMS text message: high risk, facility delivery reminders
Births with severe morbidity or mortality among all women and among those with any risk identified	Case records in the eRegistry Postpartum household survey	Registrations continuously at point of care Household visit after completion of pregnancy	Proportion with a very preterm birth, very low birth weight, perinatal death, or hospitalization of the newborn for at least 7 days after birth among all women enrolled in the trial, and those with any identified risk during ANC	Health worker clinical decision support Targeted client communication via SMS text message: referral reminders
Severe postpartum anemia	Postpartum household survey	Household visit after the completion of pregnancy	Proportion of women with severe anemia in postpartum	Health worker clinical decision support Targeted client communication via SMS text message: referral reminders

^a^ANC: antenatal care.

^b^eRegistry: electronic registry.

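### Successful referral and facility delivery are measured only among women referred or risk-identified after randomization, so these contrasts (and the risk-identified morbidity subset) are not randomized comparisons and can be biased either way

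*Protocol article*

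**What the plan says.** The denominators are set in the protocol article, Outcomes, Table 3:

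- **Successful referral:** "Proportion of women that received additional care during pregnancy among those that are referred for severe anemia, or hypertension or diabetes during pregnancy".
- **Facility delivery:** "Proportion of women that deliver in a facility among those that should delivery in a facility based on certain risk factors identified during ANC".
- **Severe morbidity or mortality:** two denominators, "among all women enrolled in the trial, and those with any identified risk during ANC".

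The section Intervention Arm describes what only that arm receives: "The decision support comprised referral and counseling reminders, medication alerts, and scheduling", and dashboards with indicators that include "screening and management of gestational diabetes, hypertension, and anemia". Under Control Arm, users there see only the records they entered themselves. Table 3 names decision support as acting directly on all three outcomes. In Table 2, referral for high blood pressure is part of a primary outcome, and Sample Size powers that composite for a rise from 12% to 22%.

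Statistical Methods promises intention-to-treat comparisons for every outcome. Its only adjustment rule concerns baseline imbalance. Referral and facility delivery have no all-enrolled version.

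**The concern.** A woman enters the denominator for the first two outcomes, and for the morbidity subset, only after a health worker has found a risk or made a referral. Both happen after allocation. The reminders, the dashboards and the wider record access are all meant to make them happen more often in one arm. If they do, the intervention subset may hold more women, and women of a different kind, than the control subset. Allocation by cluster balances all enrolled women, not those who were detected. Adjusting for baseline imbalance does not repair a denominator that the treatment itself shapes.

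At stake is how these secondary results are read. Strengths and Limitations says the outcomes are meant to allow better interpretation of the effect, so readers are likely to take the conditional ratios as intervention effects.

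**Working it through.** **The plan's own figure.** The protocol gives no rates or power for these three outcomes. Its only power statement (more than 80%) concerns the two primary outcomes. It reproduces: the design effect is 1 + (77 − 1) × 0.1 = 8.6, so the effective sizes are 29 × 77 / 8.6 = 259.7 and 30 × 77 / 8.6 = 268.6. With an assumed two-sided alpha of 0.05, power is 92.5% for 20% vs 33% and 86.6% for 12% vs 22%. The point below does not touch that figure.

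**The identity.** For successful referral:

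RR among referred = RR among all enrolled ÷ (referral rate in intervention ÷ referral rate in control).

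The conditional ratio therefore falls below 1 whenever referral rises proportionately more than the number of women who receive care.

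**Example for referral (all inputs assumed).** Per 1000 enrolled women in each arm there are 40 severe and 60 milder high-risk cases. Uptake after referral is 80% in severe and 40% in milder cases, the same in both arms.

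| | Control | Intervention |
|---|---|---|
| Referred, severe | 90% × 40 = 36 | 95% × 40 = 38 |
| Referred, milder | 20% × 60 = 12 | 80% × 60 = 48 |
| All referred | 48 | 86 |
| Received care | 36 × 0.8 + 12 × 0.4 = 33.6 | 38 × 0.8 + 48 × 0.4 = 49.6 |
| Among referred | 33.6 / 48 = 70.0% | 49.6 / 86 = 57.7% |
| Among all enrolled | 3.36% | 4.96% |

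RR among referred = 57.7 / 70.0 = 0.82. RR among all enrolled = 49.6 / 33.6 = 1.48. Check by the identity: 1.48 / (86 / 48) = 0.82.

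**Sensitivity.**

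- *Smaller or larger shift.* Keep severe referral at 90% and raise only milder-case referral from 20% to between 30% and 100%. RR among referred runs from 0.95 to 0.79, and RR among all enrolled from 1.07 to 1.57.
- *Intervention also raises uptake by 5 points.* Care received is 38 × 0.85 + 48 × 0.45 = 53.9. RR among referred = (53.9 / 86) / 0.70 = 0.90; RR among all = 53.9 / 33.6 = 1.60.
- *Uptake 60% in both strata.* With referral at 90%/20% vs 90%/80%, the arms show 28.8 / 48 and 50.4 / 84, both 60%. Nothing reverses, but the rise from 28.8 to 50.4 women reached per 1000 is invisible.

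**Facility delivery (assumed).** Delivery in a facility is 80% in severe and 50% in milder cases, whether or not risk is identified. Identification is 90% of severe cases in both arms, and 20% vs 80% of milder cases.

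- Control: (36 × 0.8 + 12 × 0.5) / 48 = 34.8 / 48 = 72.5%.
- Intervention: (36 × 0.8 + 48 × 0.5) / 84 = 52.8 / 84 = 62.9%.
- All 100 high-risk women: (40 × 0.8 + 60 × 0.5) / 100 = 62% in both arms.

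The apparent fall comes from case mix alone.

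**Risk-identified morbidity subset (assumed).** Event risk is 20% in severe and 5% in milder cases, with the same identification rates.

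- Control: (36 × 0.20 + 12 × 0.05) / 48 = 7.8 / 48 = 16.3%.
- Intervention: (36 × 0.20 + 48 × 0.05) / 84 = 9.6 / 84 = 11.4%.
- All 100 high-risk women: (8 + 3) / 100 = 11% in both arms.

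Here the artefact looks like benefit.

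**The case against.** A reader might infer that all three outcomes are unusable and that a benefit will appear as harm. The document does not support that, for these reasons, all of which stand:

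- **Morbidity is partly covered.** Its all-enrolled version is already planned; only the subset version is exposed, and there the likelier error is a spurious benefit.
- **Sign and size are unknown.** No arm-specific identification, referral or completion rate is given. A reversal needs the additional women referred to have lower uptake than those who would be referred anyway. The intervention also acts on completion, through SMS messages that support referral, which pulls the other way.
- **Facility delivery is less clear-cut.** The qualifying risk factors are not listed. If they are history items, one rule could be applied to recorded data in both arms. The outcome's row title and the phrase "among those that should delivery in a facility based on certain risk factors identified during ANC" point instead to what staff advised or found, so this is an ambiguity and not an answer.
- **Impact is bounded.** These are secondary outcomes. Better hypertension referral would partly show in a primary outcome, though referral for anemia and diabetes has no such cover.

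An all-women denominator also changes the question, since facility-delivery reminders go only to women advised to deliver in one. That weighs on the choice of remedy; it does not make the conditional contrast a randomized one.

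**Conclusion.** The concern holds for successful referral and facility delivery, which exist only as proportions within subsets formed after randomization, and for the risk-identified version of severe morbidity or mortality. What is firm is structural: the intervention targets the events that define these denominators, and nothing in Statistical Methods deals with that.

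Direction and size are not established. Under the assumed inputs, RR among referred is 0.82 against 1.48 among all enrolled. The smaller and larger shifts give 0.95 against 1.07 and 0.79 against 1.57, and equal uptake across severity gives no reversal. The artefact can also favour the intervention, as in the morbidity subset (16.3% vs 11.4% with no true effect). The primary outcomes' power and the all-enrolled morbidity outcome are not affected. The definitions should be changed, but the point does not threaten the trial's main conclusion.

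**What to change.** 1. For referral and facility delivery, make the inferential comparison among all allocated women with outcome data: referred and received additional care; delivered in a facility. The alternative is a high-risk subset defined by characteristics fixed at registration, or ascertained identically in both arms regardless of what ANC staff identified.
2. Name the all-enrolled version of severe morbidity or mortality as the inferential one.
3. Keep the present conditional proportions as descriptive steps in the care cascade, with the numbers referred or risk-identified shown by arm.
4. Record the change as an amendment to the registration, the route the protocol already uses for secondary outcomes, before actual allocations are used in the analysis.

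**Costs.** No new participants are needed, but the change is not free. Absolute proportions become smaller and rarer outcomes less precise. Effects aimed at high-risk women are diluted. Completed but unnecessary referrals count as successes. The survey-based components exist only for the surveyed subset of registered pregnancies, from June 2019 onward (Data Collection, Overview), so the denominator is women with outcome data and not everyone enrolled. Whether the survey can define a high-risk subset depends on its questionnaire, which is in an appendix not shown.
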